#### Phase 2: pre-implementation assessment

##### Objectives

To identify barriers and facilitators for the PICU Liberation program; to assess organisational readiness and parent satisfaction with current care practice; to collect baseline data of primary and secondary outcomes.

Activities:Assess barriers and facilitators for the PICU Liberation program using mixed methods, including targeted questionnaires, focus and expert group feedback.Assess knowledge and perception (acceptability) of the PICU Liberation bundle by staff as well as level of engagement of PICU clinicians.Assess organisational readiness (including teamwork and collaboration) and resource availability for implementing the PICU Liberation program (including education and training group activities, unit specific requirements including ability of the electronic medical record system to capture goals, and organisational readiness including culture and acceptability of concepts including inclusion of parents at ward rounds and other systems, settings and processes).Assess consumer engagement strategies and communication materials, ward round tools.Assess staff wellbeing (including retention).

To limit the Hawthorne effect, PICU staff will not be actively notified of the study during this time, nor will they be instructed on PICU Liberation [18]. Methods to measure baseline rates of correct assessments for pain, level of sedation, delirium, and occurrence of PICU related complications will be established (covering activity levels, over-sedation, withdrawal, delirium, PICU acquired weakness, ventilator free days, VAP, CLABSI, immobility, CAUTI, falls, mediation errors, PICU readmission, accidental line removal) (see Table 3).

**Table 3 Tab3:** A2F bundle [16] vs PICU LIBERATION bundle element specifics and measures (adapted from PUN et al. where able) [16]

Bundle element	Adult A2F bundle	PICU LIBERATION bundle	Measures

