C – Choice of sedatives	PAD guidelines - agitation/sedation assessments using a valid and reliable instrument.	Institutional analgesia and sedation guidelines – • Discourage use of sedatives, only second-tier treatment in the management of an agitated, ventilated patient; benzodiazepines, chloralhydrate and ketamine discouraged unless clinically indicated • Assessment of sedation, agitation or arousal recommended at least fourth hourly, using the Richmond Agitation and sedation scale (RASS) [29]	Instances of • RASS assessments/ opportunities • Sedation goal set/ opportunities • Sedation titration performed appropriately/ opportunities • Number of patients with “deep sedation” (RASS > − 2) • Instances of PTSS • Medication side effects recorded (opioids, benzodiazepines, ketamine, chloral hydrate) • Medication errors recorded • CLABSI and CAUTI • Accidental line removal Sedative use (by number of classes of sedatives used e.g., Benzodiazepines, chloralhydrate, ketamine) Empathic questionnaire results (carers' perception of child’s sedation management)
D – Early assessment and management of delirium	PAD guidelines - delirium assessments using a valid and reliable instrument	Institutional delirium checklist and guideline – • Guide to non-pharmacological (encouraged as first option) and pharmacological delirium management strategies. • Delirium assessment recommended at least daily, using the CAP-D^38^	Instances of • CAP-D assessments/opportunities, • Delirium identified (instances), • Appropriate management plan followed/opportunities (instances of non-pharmacological interventions targeting delirium, instances of pharmacological interventions targeting delirium) • sleep adjuncts utilised (e.g. day/night routine; swaddling/nesting) Empathic questionnaire results (carers' perception of child’s delirium prevention management)

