#### Phase 4 - assessment of the feasibility of A2F bundle adaptation and the implement success of the PICU liberation program

##### Objectives

Assess feasibility, adherence, acceptability, and impact of pilot study roll-out including on PICU related complications.

Activities:Assess the feasibility of adapting the A2F bundles in PICU.Measure bundle fidelity (i.e. bundle compliance/adherence), using both quantitative analytic and qualitative methods (Table 2, Table 4). If a low degree of fidelity of certain PICU Liberation bundle elements is present, or concerns regarding fidelity are identified, modifications to the bundle elements will be considered to maintain the bundle integrity and primary objective of the PICU Liberation program, i.e., improve patient outcomes.Compare PICU-related complication rate between from pre- (before period) and post-implementation (intermediate and after periods, refer to Fig. 3).Conduct focus groups to ascertain learnings from the implementation process and gather feedback from PICU staff about successes and areas for improvement to inform further adaptation, if required.

**Table 4 Tab4:** Definitions of PICU Liberation program: Bundle Performance and Daily Goals (adapted from PUN et al.) [16]

Element	Days eligible	Performance in the last 24 h it was documented that the patient received	Performance in the last 24 h it was documented on the daily goal checklist
A	All days	≥ 6 pain assessments using the FLACC assessments [26, 27]	FLACC goal
B1	Only days when patient received continuous or intermittent sedation	A spontaneous awakening trial (SAT) if receiving continuous or intermittent sedative infusions OR sedation target set as “light” in the daily goals	Suitability for SAT if receiving continuous or intermittent sedative infusions OR suitability for sedation goal set as “light”
B2	Only days when patient was on ventilatory support	A spontaneous breathing trial (SBT) if receiving invasive ventilation	Suitability for SBT if receiving invasive ventilation
B3	Only days when patient was on ventilatory support	An extubation assessments if receiving invasive ventilation	Suitability for extubation assessments if receiving invasive ventilation
C	All days	≥ 6 agitation-sedation assessments using the RASS (Richmond Agitation-Sedation Scale [29]	RASS goal
D	All days	≥ 1 delirium assessments using the CAP-D [31]	CAP-D requested

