### Statistical analysis

#### Sample size

The study follows a prospective before-after hybrid trial-and-implementation approach, whereby efficacy data will be collected in a convenience sample of 1800 patients (estimated) and implementation and process data will be collected from PICU staff and parents over the three-year period.

This relatively large sample of 1800 instances of complete or partial bundle implementation effects will allow an in-depth analysis of the methods considering the relatively large heterogeneity of the study population.

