Second, the PICU Liberation program is not amendable to randomisation or blinding of patients, family, or clinicians. The achieved Liberation assessments and interventions will be recorded by the bedside nurse who is unblinded and part of the intervention. The PICU Liberation facilitator will record achieved Liberation interventions during regular afternoon Liberation check-ins.

Third, to achieve the daily Liberation targets, we do not add additional people resources. This is a setting where current mobilisation, sedation, and ventilation goals are occasionally difficult to achieve. The Liberation bundle, we feel, is complementary to nursing philosophy and will be seamlessly integrated into their system with minimal, if not positive, impact on their workload. It is acknowledged, however, that this budget-neutral approach may not enable effective operationalisation of PICU Liberation, and a dedicated Liberation clinical team may be necessary.

Lastly, successful bundle adoption will create a culture shift from immobilised, sedated patients with limited family presence to comfortable awake patients who are cognitively engaged, and mobile with family members. This highlights a further limitation as bedside nurses become more comfortable applying those principles to all their patients over time, effect size may vary and increase over time, which may lead to a type II error. The high sample size and long post implementation measurement phase of 12 months may help to minimise this.

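### Table 3 defines deep sedation as RASS > −2, a rule that cannot identify deeply sedated children and makes this measure invalid if coded as printed

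*Protocol article*

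**What the plan says.** In Table 3 (Phase 2), the measures for element C include one that opens "Number of patients with “deep sedation” (RASS" and, with its cut-off, reads "Number of patients with “deep sedation” (RASS > − 2". This is the only numerical definition of deep sedation in the article, and nothing elsewhere corrects it. The same row recommends scoring at least every four hours, "using the Richmond Agitation and sedation scale (RASS".

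The Phase 2 text names the complications to be measured, "covering activity levels, over-sedation, withdrawal, delirium, PICU acquired weakness" among others, and refers to Table 3 for them. Phase 4 then plans to "Compare PICU-related complication rate between from pre- (before period) and post-implementation". The section on impact measures puts the metrics described in Table 3 on control charts and lets education and tactics respond to what the charts show.

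The intended direction is clear. In Table 4, element B1 can be met by a "sedation target set as “light” in the daily goals". The Discussion expects "a culture shift from immobilised, sedated patients with limited family presence to comfortable awake patients".

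**The concern.** The label and the rule disagree. Deep sedation is one end of a scale that runs from agitation to sedation. A rule that accepts everything above −2 accepts the neutral point and all positive scores, so it cannot pick out that end.

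Over-sedation is among the complications the programme sets out to reduce, and this is the only measure in the article that attaches a RASS value to it. If the database query or control-chart code follows the printed symbol, the indicator labelled deep sedation will count mainly children who are not deeply sedated. Staff who steer implementation by the chart, and readers of the before-after comparison, would then be looking at the wrong group.

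**Working it through.** No sample size, power or alpha enters. The article's only sample-size statement is a "convenience sample of 1800 patients (estimated", and the point does not depend on it. The check is to list which scores meet the rule and then see how the measure behaves when sedation lightens.

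**Inputs.** From the article: the rule RASS > −2; one scale for agitation and sedation; scoring at least every four hours; a PICU stay of at least 24 h for inclusion (Table 1). Assumed, because the article does not print the scale: integers from −5 to +4, negative = sedated, 0 = alert and calm, positive = agitated.

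**Step 1: which scores qualify.**
- Printed rule, > −2: {−1, 0, +1, +2, +3, +4}, 6 of 10 levels.
- Reversed, < −2: {−5, −4, −3}, 3 of 10 levels.
- Reversed, ≤ −2: {−5, −4, −3, −2}, 4 of 10 levels.

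The printed set shares no level with either reversed set.

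**Step 2: does this hang on the assumed orientation?** Mirror the scale (−4 to +5, sedation positive). Then > −2 selects −1 to +5, 7 of 10 levels, including the neutral point and one agitated level. The rule fails to isolate deep sedation either way.

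**Step 3: if each child is classified by a single score.** The shares below are illustrative and not from the article. The share at exactly −2 is held fixed at 10%, 15% and 10%.

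| Scenario | Printed, > −2 | Reversed, < −2 | Reversed, ≤ −2 |
|---|---|---|---|
| 1 | 50% to 70%, ratio 1.40 | 40% to 20%, ratio 0.50 | 50% to 30%, ratio 0.60 |
| 2 | 55% to 70%, ratio 1.27 | 30% to 15%, ratio 0.50 | 45% to 30%, ratio 0.67 |
| 3 | 30% to 60%, ratio 2.00 | 60% to 30%, ratio 0.50 | 70% to 40%, ratio 0.57 |

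On this reading the printed measure rises whenever sedation lightens.

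**Step 4: if any one qualifying score is enough.** Four-hourly scoring gives 24/4 = 6 scores in the first day. Treating scores as independent, a rough simplification, the chance of at least one score above −2 is 1 − (1 − p)^6, where p is the share above −2.
- Scenario 1: 1 − 0.5^6 = 98.4% before and 1 − 0.3^6 = 99.9% after.
- Scenario 3: 1 − 0.7^6 = 88.2% before and 1 − 0.4^6 = 99.6% after.

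Scores within a child are correlated, which lowers these figures, and longer stays raise them. The measure tends to saturate and says little about either period.

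**Step 5: the summary rule still matters once the sign is corrected.** In scenario 1 with < −2 and any one of six scores, the measure goes from 1 − 0.6^6 = 95.3% to 1 − 0.8^6 = 73.8%, ratio 0.77, where the single-score reading gives 0.50. The direction is right, but the size depends on a choice the article does not state.

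**The case against.** The strongest reply is that this is shorthand. The words deep sedation stand beside the symbol, every other part of the article treats lighter sedation as the goal, and the authors very probably meant deeper than −2. An analyst would have to follow the symbol against the label to go wrong, and nothing shows that anyone has. That is fair as to intent. It does not repair the definition: code applies the symbol, and a reader cannot tell which rule was coded or whether −2 is included. The point is also not an omission that an analysis plan might fill, since the protocol states the rule and states it wrongly.

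Three other parts of the reply stand:
- This is one item among many in Table 3. Feasibility and fidelity in Table 2 rest on bundle compliance, and element C in Table 4 counts RASS assessments without using this cut-off.
- The scale range comes from outside the article and has to be carried as an assumption.
- A reader might infer that the study would necessarily record success as harm. The documents do not support that. The measure counts patients, each with many scores, and no rule says how many must qualify. Step 4 shows it could saturate instead of reversing.

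A reader might also take element B1 in Table 4 as a second instance of the error. It is not. It gives no RASS value for a light target and shows only what the programme intends. Likewise, the link from over-sedation in the Phase 2 list to this bullet runs through the reference to Table 3; the article does not equate the two in words.

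**Conclusion.** The definition is wrong as printed. A rule of RASS > −2 cannot identify deeply sedated children on a scale that covers agitation and sedation, whichever way the scale runs. Under the assumed −5 to +4 range it selects −1 to +4 and excludes −3 to −5, the opposite of the label.

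If the rule is coded literally, the measure is invalid for over-sedation. With one score per child it would rise as sedation lightens, by ratios of 1.27 to 2.00 in the assumed scenarios. With any single score sufficing it would sit near its ceiling. Either way its before-after comparison and control chart could not be used.

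The damage is confined to this measure and to decisions taken from its chart. The article does not name it as a primary or feasibility outcome, so the documents do not support a claim that the study's main conclusions would reverse. Nor do they show whether the database repeats the printed sign.

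**What to change.** In Table 3, element C:
1. Reverse the inequality so that the measure captures scores deeper than the −2 cut, and state whether −2 itself counts.
2. State how a child's repeated scores become one classification, for example any qualifying score, the deepest score per day, or the share of scored days. Table 4 makes the number of RASS assessments a performance target, so an any-score rule could drift with assessment frequency even after the sign is corrected.
3. Confirm that the same coded rule is applied to the recorded RASS scores in the Before, Intermediate and After periods and behind the control charts. Re-run any chart already produced with the printed sign.

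The cost is one symbol, a sentence or two in Table 3, and a check of the extraction and chart code. Where RASS scores were recorded, the measure can be recomputed from them without new data. The change corrects an outcome definition only and sets no sedation target.

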A – Optimising analgesia	PAD guidelines - pain assessments using a valid and reliable instrument	Institutional analgesia and sedation guidelines • Stepwise introduction of analgesics first in agitated or distressed child • Assessment of pain at least fourth hourly, using the FLACC score [26, 27].	Instances of • FLACC assessments/opportunities • Appropriate stepwise use of pain medication (percentage) • WAT [28] assessments/opportunities • Withdrawal instances Opioid and benzodiazepine use Instances of expressed breast milk and sucrose utilisation for procedural pain relief (number of prescriptions and administration episodes) Empathic questionnaire results (carers' perception of child’s pain management)
B – spontaneous awakening and breathing trials	Guide for spontaneous awakening trial (SAT) if patients is receiving continuous or intermittent sedative infusions Guide for spontaneous breathing trial (SBT) if receiving mechanical ventilation	• Safety screening tool and checklist for SABT adapted for PICU to guide nurse-led SABTs • Safety screening tool and checklist for extubation readiness adapted for PICU to guide nurse enabled extubations	Instances of • SABT screening performed/opportunities, • SABT trials/opportunities, • Extubation assessments/opportunity, • Instances of nurse-enabled extubation/opportunity • Ventilator associated pneumonia • Failed extubations, accidental extubations requiring re-intubation within 1 h • Delay from extubation ready to time of extubation Hours/days without invasive ventilation Empathic questionnaire results (carers' perception of child’s spontaneous awakening and breathing trials)

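### Medication side effects are counted only for opioids and the three sedatives the bundle discourages, so the count cannot separate less drug harm from a move to unlisted drugs

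*Protocol article*

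**What the plan says.** All of the key text is in Table 3 of the protocol article, in the rows for elements A, C and D.

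- **Harm measure, element C:** "Medication side effects recorded (opioids, benzodiazepines, ketamine, chloral hydrate"). There is no *e.g.* and no category for other drugs.
- **Guidance in the same row:** "Discourage use of sedatives, only second-tier treatment in the management of an agitated, ventilated patient", followed by "benzodiazepines, chloralhydrate and ketamine discouraged unless clinically indicated".
- **Use measure in the same cell:** "Sedative use (by number of classes of sedatives used e.g., Benzodiazepines, chloralhydrate, ketamine"). This one is open-ended.
- **Element A:** "Stepwise introduction of analgesics first in agitated or distressed child".
- **Element D:** "Guide to non-pharmacological (encouraged as first option) and pharmacological delirium management strategies". Its measures include "instances of pharmacological interventions targeting delirium", but no side effects of those drugs.

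The Data collection section cites Table 3 among the sources of data for the before, intermediate and after periods. The section on impact measures says that process-of-care outcomes are assessed before and after implementation. The Phase 3 text says that safety metrics are monitored and reported to staff, without naming them.

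**The concern.** The list of drugs whose side effects count is tied to the intervention. The bundle steers staff away from three named sedatives, and those three are the only sedatives whose side effects are recorded. Any use that moves to a drug off the list leaves the numerator, whatever harm that drug causes.

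Sedatives are not abolished. They remain available as a later step, and element D provides for drug treatment of delirium. Drugs outside the list may therefore be given under the bundle, and the open-ended sedative-use measure itself allows for other classes.

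A lower side-effect count after implementation could then be read as a safety gain when it partly reflects which drugs were counted. Adjustment for prognostic factors cannot repair this, because the missing events were never recorded.

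**Working it through.** The article gives no figure for this measure, so there is none to reproduce. The check compares the lists and then shows what follows under stated assumptions.

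**Step 1: compare the lists in Table 3.**

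| Drug group | Discouraged by name | Side effects counted |
|---|---|---|
| Benzodiazepines | yes | yes |
| Ketamine | yes | yes |
| Chloral hydrate | yes | yes |
| Opioids | no | yes |
| Other sedatives | as a class only | no |
| Non-opioid analgesics | no | no |
| Delirium drugs not listed above | no (non-drug measures encouraged first) | no |

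**Step 2: effect of a switch on the count.** Assumed inputs, none of them in the article:

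- p: share of counted Before-period events due to the three listed sedatives, the rest being due to opioids
- s: fraction of that sedative use that moves to unlisted drugs
- k: side-effect risk on the unlisted drugs relative to the listed sedatives
- all Before-period side effects come from listed drugs, and opioid events do not change

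Counted ratio (after/before) = (1 - p) + p(1 - s) = 1 - p*s.
True ratio = 1 - p*s + p*s*k, which is 1.00 when k = 1.

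Counted ratio when the true ratio is 1.00:

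| p | s = 10% | s = 25% | s = 50% |
|---|---|---|---|
| 25% | 0.975 | 0.9375 | 0.875 |
| 50% | 0.95 | 0.875 | 0.75 |
| 75% | 0.925 | 0.8125 | 0.625 |

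**Step 3: the same count fits different truths.** Take p = 50% and s = 25%, so p*s = 0.125 and the counted ratio is 0.875 throughout.

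- Use stopped and not replaced (k = 0): true ratio 1 - 0.125 = 0.875, a real fall
- Replaced at half the risk (k = 0.5): 0.875 + 0.0625 = 0.9375
- Replaced at equal risk (k = 1): 0.875 + 0.125 = 1.00
- Replaced at twice the risk (k = 2): 0.875 + 0.25 = 1.125, a rise

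**Step 4: the net direction is not fixed.** If opioid events rise by a fraction g, the counted ratio is p(1 - s) + (1 - p)(1 + g). With p = 50%, s = 25% and g = 25%, it is 0.375 + 0.625 = 1.00. A rise in counted opioid events can cancel the apparent fall.

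**The case against.** **Substitution is not documented.** The article names no replacement drug. It discourages sedatives as a class, puts analgesics first, and prefers non-drug management of delirium. A reader might infer that the bundle itself moves exposure off the list and that the measure is therefore biased in its favour. The text does not support that as a fact. Less sedation overall would be a real benefit, a shift to opioids would still be counted, and Step 4 shows that the net sign depends on drug use the article does not give. This part of the objection stands, and the point is conditional on a switch.

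**Size.** A reader might apply the switch to every listed event and infer a fall of 25% to 50% at s = 25% to 50%. That sets p = 100% and treats opioids as discouraged, which they are not by name. Only the non-opioid share is exposed to this switch.

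**Role of the measure.** It is one Table 3 item. It is absent from the list of PICU-related complications under Phase 2, and the Phase 4 comparison is of that complication rate. Nothing says it is among the safety metrics reported in Phase 3. This limits the importance of the point.

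**Other measures.** Number of sedative classes, drug treatment of delirium, "Medication errors recorded", withdrawal, deep sedation, delirium and accidental line removal carry no restriction to the four listed groups. It would therefore be too strong to say that harm from substitutes goes wholly unseen. Still, none of these counts side effects of unlisted drugs.

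**Closed list.** The case report form is not shown and may be wider. But the list is stated content, and the neighbouring measure in the same cell has an *e.g.* where this one has none.

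**Conclusion.** The point holds in conditional form. As written, the measure covers opioids and the three discouraged sedatives only, so it cannot distinguish a real fall in drug harm from a move to unlisted drugs. With a true ratio of 1.00, the counted ratio is 1 - p*s. Over the assumed range in the table it runs from 0.975 to 0.625, with 0.875 at p = 50% and s = 25%. The article gives neither p nor s, so the actual size is unknown and may be zero if no switch occurs.

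The conclusion rests on reading the list as complete and on no other part of the plan recording side effects of other drugs. It affects one secondary safety measure, not the feasibility outcomes or the listed PICU-related complications. It is worth correcting because the remedy is specific and cheap.

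**What to change.** 1. In Table 3, element C, and on the case report form, record side effects for every analgesic, sedative and delirium drug given, with the same definition and record source in all periods.
2. The Before period (March 2019 to March 2020) closed before the trial was registered in October 2021. Extract its unlisted drugs from existing records where possible.
3. Use the total across all drugs, per patient or per PICU patient-day, as the before/after measure. Give rates by class per exposed day only as a supplement. On its own, an exposed-day denominator would hide the benefit of using less drug: if exposure and events both halve, the rate is 0.5/0.5 = 1, unchanged.
4. If the Before period cannot supply the unlisted drugs, state that the measure covers listed drugs only and cannot show net drug safety.

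**Cost:** one table line, a form field, a wider data extraction, and a comparison that may look less favourable. The change concerns measurement only and takes no view on which drugs should be used.

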### Implementation process

#### Phase 1: bundle adaptation to Australian PICU context

##### Objectives

To adapt the ICU Liberation A2F bundle to PICU through identification of specific requirements for children necessitating special consideration within the A2F bundle elements. To account for further neuroscientific developmental stages, each bundle element will then be adapted for infants ≤6 months of age in the “Baby-Liberation” program.

Activities:Comparison of current practice and Liberation model of care to identify gaps and areas for improvement required. Current assessment tools and documentation will be workshopped, and results will inform the development of the nurse-led, interdisciplinary PICU Liberation model of care.Comprehensive review of the current clinical assessment tools, guidelines and documentation (e.g., pain assessment, sedation assessment) to identify and remove duplicates, and to add updated and evidence-based assessment tools and guidelines where needed.A series of focus groups and workshops to discuss and gather feedback on the acceptability of the PICU Liberation bundle elements (see Fig. 2), and the proposed education tools developed by the PICU Liberation program implementation group.Assessment of any specific bundle requirement for use in specific patient cohorts; for example, neonates and infants less than 6 months of age.Regular assessment and revision (when appropriate) of the adapted PICU Liberation elements and contents will occur. A feedback and evaluation process will be established and include clinician and family feedback, audits, and evaluations (Table 2). Survey analyses and feedback from experienced clinicians that will be engaged to help improve each bundle element based on learnings from “provide care as required” will inform changes required as well.The four study phases will include parent/carer and clinician engagement workshops.Ongoing modifications to the PICU’s Clinical Information System to streamline documentation, to add assessment pieces where required for new content (e.g., early mobility assessment), and ensure all documentation is purposeful for clinical decision-making.

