#### Descriptive statistic analyses

The twelve pre-implementation-months will be collated and presented as a single timeframe; all months during the implementation period will be described separately. Categorical variables will be described as counts (percentage). Continuous variables will be described by their median (interquartile range). Continuous outcome measures such as the length of stay (LOS) and hospital free days will be analysed using either survival analysis and competing-risks regression. The availability of recorded data on a specific characteristic will be described (e.g., we can only describe sedation on days which had any sedation data recorded).

In addition to analysis of the whole patient cohort, we will undertake sub-analyses for patients < 6 months of age, PICU stay shorter than 48 h and non-ventilated patients.

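### Delirium and deep sedation are counted with tools whose frequency the bundle raises, and the before/after comparison takes no account of how often children were assessed

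*Protocol article*

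**What the plan says.** All references are to the protocol article.

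- **Outcomes.** Phase 2 lists the PICU-related complications to be measured, "covering activity levels, over-sedation, withdrawal, delirium, PICU acquired weakness" among others, and refers to Table 3 for the measures.
- **Comparison.** Phase 4 plans to "Compare PICU-related complication rate between from pre- (before period) and post-implementation (intermediate and after periods, refer to Fig. 3)". The section on impact measures adds absolute and relative risks, then logistic regression for prognostic factors. It gives acuity and staffing ratios as examples of confounders to monitor.
- **How cases are counted.** Table 3, row D, lists CAP-D assessments over opportunities and then "Delirium identified (instances)". The assessments have an opportunities denominator; the identified cases do not. Row C counts patients with deep sedation by RASS. Row A lists WAT assessments over opportunities and, separately, "Withdrawal instances".
- **What the bundle changes.** Table 3 recommends CAP-D at least daily and RASS at least fourth hourly. Table 4 scores performance as at least one CAP-D and at least six RASS assessments in 24 hours, on all days. Table 2 defines fidelity as 75% or more, and/or an improvement of 25% or more over baseline.
- **Baseline.** Staff are not instructed on the programme in Phase 2. Phase 1, which also lies in the Before period, plans "to add updated and evidence-based assessment tools and guidelines where needed".
- **Missing assessments.** The descriptive section will describe data availability, for example "we can only describe sedation on days which had any sedation data recorded".

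**The concern.** A case of delirium or deep sedation enters these counts when a tool is applied and scores positive. Applying CAP-D and RASS more often is something the programme sets out to do. If it succeeds, recorded cases can rise with no change in the children's condition, and the better the implementation, the larger the artefact. A real benefit could be diluted, hidden or reversed.

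This matters beyond the final report. Phase 3 adapts the bundle partly on its effects on complication rates, selected patient outcomes are shown live to clinicians, and the economic analysis costs PICU-related problems.

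**Working it through.** The article gives no event rate, baseline coverage or expected effect, so there is no figure of the plan to reproduce. What follows illustrates direction and range.

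**Inputs for delirium.**
- True proportion with delirium: 30% (assumed).
- After-period screening: 75% of days. This borrows the Table 2 fidelity threshold; that CAP-D coverage would equal it is an assumption.
- Before-period screening: 25%, 50% or 60% of days (assumed).
- Delirious days per affected child: 1, 2 or 3 (assumed). The test is taken as perfect and screening as random over days.

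**Formula.** With daily screening probability s and m delirious days, detection = 1 − (1 − s)^m, and observed proportion = true proportion × detection.

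**Two ends of the range, no true effect.**
- m = 1, screening 25% to 75%: 0.30 × 0.25 = 7.5% before and 0.30 × 0.75 = 22.5% after; apparent RR 3.0.
- m = 3, screening 60% to 75%: detection 1 − 0.4³ = 0.936 and 1 − 0.25³ = 0.984; observed 28.1% and 29.5%; apparent RR 1.05.

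Apparent RR with no true effect:

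| Before-period screening | m = 1 | m = 2 | m = 3 |
|---|---|---|---|
| 25% | 3.00 | 2.14 | 1.70 |
| 50% | 1.50 | 1.25 | 1.12 |
| 60% | 1.25 | 1.12 | 1.05 |

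The m = 1 column also describes a count of positive patient-days over all patient-days, because that ratio is simply the ratio of coverages.

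**With a true fall from 30% to 20% (true RR 0.67).** For m = 1 the apparent RR is 2.0, 1.0 or 0.83 in the three rows; for m = 3 it is 1.14, 0.75 or 0.70.

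**Chance of a significant but spurious increase.** If the planned 1800 patients split 900/900 (assumed), a two-sided 5% test with no true effect has these probabilities of significance: 1.00, 0.98 and 0.66 for m = 1, and 1.00, 0.34 and 0.10 for m = 3.

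**Deep sedation.** Let q be the chance that a single reading is deep and k the readings per day. P(at least one deep reading) = 1 − (1 − q)^k. With q = 5% (assumed):
- k = 2: 1 − 0.95² = 9.8%.
- k = 6 (the Table 4 standard): 1 − 0.95⁶ = 26.5%.

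Both days count as having sedation data, so restricting to recorded days does not remove this effect.

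**The case against.** The case on the other side has weight.

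- **The ingredients for a correction are planned.** Assessments over opportunities are in Table 3, baseline rates of correct assessments are to be measured in Phase 2, and data availability will be described. A condensed article may leave denominators to a fuller plan. This stands in part: it makes the fix cheap. But the article itself sets out the outcome counts, the bundle's assessment frequencies and the comparison, names other adjustment factors, and does not link coverage to the comparison.
- **The limitations are candid.** The Discussion admits unblinded recording by bedside nurses, and the methodological limitations mention missing data. Neither says that the amount of assessment is expected to differ by period because of the intervention.
- **The effectiveness results are modest in status.** Feasibility is the first hypothesis, and bundle effects are described as preliminary. This stands, and limits the stakes.
- **The bias may be small.** This also stands. Some sedation assessment already existed, since Phase 1 lists it among current tools, and with several delirious days most cases are found in either period.

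A reader might infer more than the text supports. That withdrawal is equally affected is not shown: WAT is tracked in Table 3 but has no stated frequency there and is absent from Table 4. Physical function (cCPAx) does not belong in the point: it too has no stated frequency, and Table 4 scores a mobility activity instead. Nor does the article say that these tools are the sole route of detection; it simply states no other, and Fig. 3 and Appendix 1 are not shown. That before-period assessments went mainly to children already suspected of a problem is possible, but nothing in the article establishes it.

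**Conclusion.** The point holds for delirium by CAP-D and deep sedation by RASS. Followed as written, the comparison cannot separate a change in occurrence from a change in assessment. For raw counts, more assessment in the later periods works against the bundle.

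The size cannot be determined from the article. Under the stated assumptions the apparent delirium RR with no true effect lies between about 1.05 and 3.0, and the daily chance of at least one deep reading moves from 9.8% to 26.5% between two and six readings. Quoting only the upper end as the expected bias would be wrong. The conclusion also assumes that assessment frequency actually rises, which is the design intent and not yet an observed fact. For withdrawal it remains an inference. This is a worthwhile improvement to the analysis; it does not invalidate the study, and it is no reason to remove delirium as an outcome.

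**What to change.** 1. **Delirium:** compare CAP-D-positive patient-days per assessed patient-day.
2. **Over-sedation:** compare the proportion of RASS readings in the deep range, or standardise to the same number of readings per day in each period. A rate per assessed day is not enough here, because a day with one reading and a day with six would count alike.
3. **Coverage:** show assessment coverage by period and month beside every such rate, including within the Before year, when tools may change.
4. **Unassessed days:** add sensitivity analyses. With coverage c, rate p on assessed days and rate k × p on unassessed days, the overall rate is p × [c + (1 − c) × k]. Use values of k below and above 1, and let k differ by period, since before-period assessment may have been selective. Setting k = 0 only returns the raw rate, and k = 1 only the assessed-day rate, so these two values alone do not bound the answer.
5. **Reporting:** state differential detection as a limitation. Read delirium and over-sedation alongside outcomes already collected that do not depend on the bundle's tools, such as ventilator-free days, length of stay, CLABSI and readmission. Apply the same caution to withdrawal if WAT coverage proves to differ between periods.

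The assessment counts are already to be collected, so the cost is extra analysis work and more cautious claims for delirium and over-sedation.
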